#### Recruitment, Inclusion, Allocation, and Blinding of Patients

Patients will be recruited for study participation when they are on the waiting list in one of the participating hospitals and will receive a study information letter on behalf of their doctor. Contact will be made by phone to check their willingness to participate and to access eligibility. Eligible patients willing to participate will be included. After the patient completes the baseline questionnaire T(0) within 2 week before surgery and has signed informed consent, randomization will be executed by an (independent) research assistant. A computer-generated randomization in a 1:1 ratio will be performed on individual level stratified regarding hospital, sex, and surgical procedure using permuted blocks of size 2. Patients will be blinded to the intervention, as they do not know which program is developed as a nonintervention or intervention care program. The researchers involved in the analyses will be blinded to the allocation throughout the analyses. Health care professionals cannot be blinded to the intervention because it is highly likely that they will be notified of the allocation either by the patient or the patients’ medical file.

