### Step 5: Program Implementation Plan

Patients undergoing major abdominal, general surgical, or gynecological procedures were identified as new program users. No new professionals were identified as program users as the introduction and implementation of the program would remain in the perioperative phase also for the extended patient group. The 7 hospitals that participated in the earlier performed “ikherstel” study wished to continue the use of the “ikherstel” intervention including broadening the usage of “ikherstel” intervention at the general surgery department of their hospital. Many other general hospitals in different regions in the Netherlands signed the letter of intent to participate in this multicenter study. After a kick-off meeting at the research institute, one meeting with surgeons or gynecologists (depending on the department) and one meeting with nurses per hospital was held to discuss the content and logistics of the study and its implementation. Finally, 10 general surgery practices and 8 gynecology practices (all teaching hospitals) were positive about the further development of “ikherstel” intervention and willing to implement the intervention. They will participate in the evaluation of this intervention through implementation of the eHealth intervention as a supplement to the standard perioperative care given at their hospital.

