### Step 6: Evaluation

#### Study Design

The evaluation of the eHealth intervention will be performed by a multicenter single-blinded RCT. The effectiveness and cost-effectiveness of this innovative eHealth care program compared with the usual care given in 11 participating hospitals on RNA and RTW will be evaluated. A process evaluation will also be performed using a mixed-methods design [56].

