#### Eligibility Criteria

Patients who will undergo a laparoscopic or open colectomy or hysterectomy and are aged between 18 and 75 years will be contacted. Exclusion criteria are surgery without a curative intention, deep infiltrating endometriosis, concomitant surgical procedures, not able to use the internet, unable to understand Dutch questionnaires, malignancy (in case of the hysterectomy), and receiving neoadjuvant treatment.

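### Fixed blocks of 2 in small strata let anyone who knows the block size, the entry order and the previous allocation deduce up to about half of all allocations

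*Protocol article*

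**What the plan says.** All the relevant text on allocation is in the Protocol article, section Recruitment, Inclusion, Allocation, and Blinding of Patients.

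- **Ratio and unit:** "A computer-generated randomization in a 1:1 ratio will be performed on individual level".
- **Strata and blocks:** "stratified regarding hospital, sex, and surgical procedure using permuted blocks of size 2". No variation in block size is mentioned.
- **Who randomizes, and when:** after informed consent and the baseline questionnaire, "randomization will be executed by an (independent) research assistant".
- **Staff blinding:** "Health care professionals cannot be blinded to the intervention because it is highly likely that they will be notified of the allocation". The stated routes are the patient and the medical file.
- **Recruitment:** patients come from a participating hospital's waiting list and "will receive a study information letter on behalf of their doctor". Willingness and eligibility are then checked by phone; the article does not say by whom.

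The number of strata has to be pieced together. Step 5: Program Implementation Plan lists "10 general surgery practices and 8 gynecology practices (all teaching hospitals"). Study Design refers to "usual care given in 11 participating hospitals". Eligibility Criteria covers "Patients who will undergo a laparoscopic or open colectomy or hysterectomy".

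**The concern.** A fixed block of 2 is the most predictable permuted-block scheme: every second allocation in a stratum is the opposite of the one before it. That matters little if nobody near enrollment learns earlier allocations. Here the article says that treating staff very probably will.

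The sequence is also short and local. If hysterectomy is done in the gynecology practices and colectomy in the surgery practices, a gynecology practice has one stratum and a surgery practice two (men and women). Only the last allocation in each needs to be remembered.

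What is at stake is selection at entry. Someone who expects a particular arm next could affect whether or when a patient is approached, or how strongly participation is encouraged. The primary outcome (Outcome Measures) is the patient-reported time until all of eight self-chosen activities are resumed, which plausibly depends on fitness and motivation. Neither is a stratification factor. Blinding of patients and analysts acts after enrollment and does not protect against this.

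**Working it through.** The article gives no figure for predictability, so there is none to reproduce. The total of 354 is taken as stated in Sample Size Calculation; the shares below hardly depend on it.

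**1. Number of strata (assumption).** Colectomy in 10 surgery practices for both sexes, hysterectomy in 8 gynecology practices for women only: 10 × 2 + 8 = 28 strata. Mean size is 354 / 28 = 12.6 patients.

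**2. Forced share in complete blocks.** In a 1:1 block of size 2m, the expected number of forced final allocations is 2m/(m + 1), so the forced share is 1/(m + 1):
- size 2: 1/2
- size 4: 1/3
- size 6: 1/4

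**3. Forced count with incomplete last blocks.** For size 2 the count is the sum over strata of floor(n/2).
- If about half of the 28 strata end on an odd number: (354 − 14) / 2 = 170, and 170 / 354 = 48.0%.
- If all 28 end on an odd number: (354 − 28) / 2 = 163, or 46.0%.
- Simulation with unequal stratum sizes: 48.1% (95% range 47.2% to 48.9%).

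**4. Sensitivity to the number of strata.**

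| Strata | Meaning | Simulated forced share | All strata odd |
|---|---|---|---|
| 18 | one per department | 48.7% | 168/354 = 47.5% |
| 28 | base case | 48.1% | 163/354 = 46.0% |
| 56 | if open/laparoscopic were also a factor | 46.2% | 149/354 = 42.1% |

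**5. Best-guess accuracy, size 2.** Forced allocations are guessed correctly every time, the rest half the time: 0.48 × 1 + 0.52 × 0.5 = 0.74. With no information it would be 0.50.

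**6. Allowing for imperfect knowledge.** Let q be the probability that the earlier allocation is learned before the next patient enters (not given). The deducible share is about 0.48q:

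| q | Share | Patients (170q) |
|---|---|---|
| 0.25 | 12% | about 43 |
| 0.5 | 24% | 85 |
| 0.75 | 36% | about 128 |
| 0.9 | 43% | 153 |
| 1 | 48% | 170 |

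**7. Alternatives, simulated with 354 patients in 28 strata.**

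| Block sizes | Best guess correct | SD of overall arm difference |
|---|---|---|
| 2 fixed | 74.0% | 3.8 |
| 4 fixed | 69.4% | 4.8 |
| 2/4 random | 71.0% | 4.6 |
| 2/4/6 random | 68.8% | 5.2 |

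With fixed size 4, 30.3% of allocations are still certain to someone who knows the block boundaries. With random 2/4/6, about 3.4% are (0.034 × 354 ≈ 12 patients), even if the set of sizes is known and used optimally. The SD of 3.8 for size 2 agrees with a direct check: about 14 odd strata each contribute ±1, and √14 = 3.7.

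**8. Cost of the larger imbalance.** A difference of two SDs, 2 × 5.2 = 10.4 patients, reduces statistical information by a fraction (10.4 / 354)² = 0.0009, under 0.1%.

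**The case against.** The strongest reply is that deducible is not the same as known, and that the article does not place the knowledge and the opportunity in the same hands.

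- **The 48% is conditional.** One person must know the block size, the order of entry into the stratum and the previous allocation in time. This stands, and is why the share is given as 0.48q.
- **Those who learn allocations are not shown to be those who recruit.** Staff learn through patients or files after randomization. The letter goes out in the doctor's name, but the phone screening is by an unspecified party. This stands: that clinicians steer who is approached is a possibility, not something the article states.
- **The order of events limits exploitation.** Approach, screening, consent and the baseline questionnaire, completed within two weeks before surgery, all precede randomization. Several patients of one stratum may be in progress together, so the next position in the block may be unclear. This lowers the opportunity but leaves the second allocation in each pair deducible.
- **Publication does not show that recruiters knew the block size.** The article does not say what departments were told, and it speaks of the final intervention as already used for the trial, so it may have appeared after recruitment began. This stands.
- **Adjustment is planned.** Data Analyses Plan adjusts for hospital, procedure and sex, and for clinically relevant baseline differences. That helps with measured factors but not with unmeasured motivation.
- **Best-guess accuracy improves only from 74% to 69%.** True; the main gain is in allocations that are certain, about 170 down to about 12.

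A reader might infer that half of the allocations are known in advance, or that concealment fails for every second patient. The article does not support either: q is unknown, and the recruiters' access to earlier allocations is not described.

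**Conclusion.** The point holds as an avoidable design risk. With fixed blocks of 2, up to about half of allocations can be deduced with certainty: about 170 of 354 at 28 strata, and 46% to 49% on the simulated range from 18 to 56 strata. The realistic share is about 0.48q, with q not given. The stated safeguards reduce the opportunity for selection but do not remove the deduction. The arithmetic is secure; the stratum count is an assumption to which the result is insensitive. Whether selection bias arises, and how far it would move the hazard ratio, cannot be determined from the article, and no such effect is claimed here. The change is worth making because it is cheap and blocks of 2 gain very little in balance.

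**What to change.** Replace the fixed block size with randomly varying sizes, for example 2, 4 and 6, within the same strata. Generate the list centrally and do not disclose the sizes to departments or recruiters. Minimization with a random element on the same factors is an alternative.

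The cost is a new randomization list and one protocol line. The SD of the overall arm difference rises from about 3.8 to 5.2 patients of 354, and the largest possible difference within a stratum rises from 1 to 3. The planned adjustment for hospital, procedure and sex accommodates this.

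If recruitment is under way, apply the change to the remaining list. If it is complete, report the predictability of the allocation as a limitation, with a statement of who approached and screened patients and whether they could see earlier allocations.

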#### Data Analyses Plan

All analyses will be performed in IBM SPSS. Baseline characteristics will be summarized using descriptive statistics and compared between the intervention and control group using *t* tests by normal distributions of variables and Mann-Whitney *U* tests, chi-square tests, or Fisher exact tests by non-normal distributions of variables. Our primary outcome, time until full RNA, will be analyzed by both crude and adjusted survival analyses where hospital, surgical procedure, and sex will be taken into account as covariates in the adjusted analyses due to stratification. To describe the distribution of the duration until RNA in both groups, the Kaplan Meier method will be used. The Cox proportional hazard model will be applied to calculate hazard ratios. Adjustments will be made if there are clinically relevant differences between the intervention and the control group in the baseline characteristics or if other potential confounding factors are observed. For the longitudinal secondary outcomes, mixed models and multilevel logistic regression models will be performed. For the cross-sectional secondary outcomes, *t* tests, Mann-Whitney *U* tests, chi-square tests, or Fisher exact tests will be used to compare differences. Intention-to-treat analyses will be compared with per-protocol analyses to identify whether there are differences if patients used the intervention as intended. Subgroup analyses will be performed regarding the surgical procedure (colectomy and hysterectomy) and indication (benign or malignant disease). A post hoc analysis will be carried out on patients without major complications.

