##### Developing the Materials and Tools of the Revised “ikherstel” Intervention

###### Providing Information on the Website

For patients who will receive adjuvant chemotherapy, information about this treatment, including side effects, is provided on the website. This will provide extra attention and mental support in case of patients with a malignant indication. Videos are also added on the website. Videos are considered the most appropriate medium to deliver an informative message to patients because of the influence of modeling behavior on attitude [55]. Videos about the admission day, the surgical procedures, receiving and managing a permanent or definitive stoma, the postoperative period, and a simulation of patients and employers to discuss potential RTW problems are provided.

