#### Sample Size Calculation

To detect a hazard ratio of 1.4 for RNA (corresponding to a decrease in median time to RNA from 10 weeks to 7.14 weeks as a result of the intervention) with 80% power while testing using a 2-sided log-rank test at a significance level of 5%, a total of 318 events need to be observed. The total sample size is set at 354 (177 per arm) to account for an anticipated proportion of 2.5% of patients not returning to daily activities within the 12 month follow-up period and a dropout rate of 10%.

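### Surgical procedure as a covariate in the adjusted Cox model assumes proportional recovery hazards for colectomy and hysterectomy; stratifying on it drops that assumption at almost no cost

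*Protocol article*

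**What the plan says.** The Data Analyses Plan (Step 6: Evaluation) describes time to full resumption of activities with Kaplan-Meier curves and takes hazard ratios from a Cox proportional hazards model. Crude and adjusted versions are both planned, and neither is named as the deciding one. For the adjusted version, "hospital, surgical procedure, and sex will be taken into account as covariates in the adjusted analyses due to stratification". The same section plans subgroup analyses by procedure and by benign or malignant indication.

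Randomisation is stratified by hospital, sex and procedure (Recruitment, Inclusion, Allocation, and Blinding of Patients). The Eligibility Criteria admit colectomy and hysterectomy, but the exclusions include "malignancy (in case of the hysterectomy"; colectomy for cancer stays in. The intervention text foresees some patients having chemotherapy after surgery: "For patients who will receive adjuvant chemotherapy, information about this treatment, including side effects, is provided on the website".

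The Sample Size Calculation is based on "testing using a 2-sided log-rank test at a significance level of 5" per cent and on a hazard ratio of 1.4.

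**The concern.** A procedure covariate gives every patient the same baseline hazard, scaled up or down by one constant. The hazard of resuming activities after colectomy must then stand in a fixed ratio to that after hysterectomy at two weeks, at three months and at a year. The two groups are clinically unlike, since one is all benign and the other partly malignant, so their curves could differ in shape as well as level.

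If they do, the covariate model misstates who is still at risk of recovering at each time. The treatment hazard ratio is then pulled toward 1 and some power is lost. Procedure has only two levels and is already a randomisation stratum, so a separate baseline hazard for each level is readily available.

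**Working it through.** **The two models.** With treatment x and procedure p:
- covariate: h(t) = h0(t) · exp(βx + γp + hospital and sex terms)
- stratified: h(t) = h0p(t) · exp(βx + hospital and sex terms), with a separate h0p for each procedure.

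Both assume one treatment effect β across procedures. They differ only in whether the baselines must be proportional.

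**Plan's own figure.** Inputs from the Sample Size Calculation: "To detect a hazard ratio of 1.4 for RNA", a "decrease in median time to RNA from 10 weeks to 7.14 weeks" (10/1.4 = 7.14), "with 80% power while testing using a 2-sided log-rank test", and "a total of 318 events need to be observed".
- Schoenfeld at 80% power: 4(1.960 + 0.842)²/(ln 1.4)² = 278 events.
- At 85% power: 4(1.960 + 1.036)²/(ln 1.4)² = 318 events.

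So 318 does not reproduce at 80%. That is a separate matter. Here only the benchmark is needed: 354 × 0.975 × 0.90 ≈ 310 events, and Φ(ln 1.4 · √310/2 − 1.960) = 84% power if the model is right.

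**Approximate cost of attenuation.** The same formula with 310 events gives 81% at a hazard ratio of 1.38 and 77% at 1.36.

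**Assumptions for the simulation (none are in the article).** Weibull recovery times, control medians of 12 weeks (colectomy) and 8 weeks (hysterectomy), and a treatment hazard ratio of 1.4 within each procedure. For Weibull curves the colectomy/hysterectomy hazard ratio varies as t^(kC − kH), so it is constant only when the shapes are equal. For shapes 1 and 2 it is (ln 2/12)/(2t · ln 2/64) = 2.67/t: 1.33 at week 2, 0.33 at week 8 and 0.13 at week 20.

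**Results with a 50% colectomy share.** Dropouts are removed (354 × 0.9 ≈ 319 patients). Power and null rejection come from 1,500 trials each; hazard ratios are large-sample limits. Each pair is covariate / stratified.

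| Shape, colectomy/hysterectomy | Hazard ratio | Power, % | Power lost, points | Null rejection, % |
|---|---|---|---|---|
| 1.5/1.5 | 1.395 / 1.395 | 84.3 / 83.7 | −0.6 | 5.0 / 5.1 |
| 1.2/1.8 | 1.368 / 1.394 | 81.5 / 84.1 | 2.6 | 3.5 / 4.5 |
| 1.0/2.0 | 1.363 / 1.406 | 76.9 / 82.9 | 6.0 | 3.2 / 4.9 |
| 0.8/2.5 | 1.330 / 1.392 | 74.3 / 83.2 | 8.9 | 2.3 / 4.3 |
| 2.0/1.0 | 1.384 / 1.397 | 81.5 / 83.0 | 1.5 | 6.5 / 5.7 |

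The Monte Carlo standard error is √(0.8 × 0.2/1500) = 1.0 point for a power and √(0.05 × 0.95/1500) = 0.6 point for a rejection rate. The 6.5% in the last row goes with 6.0% for the crude model on the same simulated trials, and falls to 4.7% and 4.9% at the other two shares, so I read it as noise.

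**Other procedure mixes.** At colectomy shares of 30% and 70% the loss is 2.2 and 1.7 points for shapes 1.2/1.8, 4.5 and 4.2 for 1.0/2.0, and 6.9 and 7.5 for 0.8/2.5.

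**Other dropout handling.** These runs had 177 patients per procedure and 10% random dropout over 52 weeks (covariate / stratified):
- equal shapes: hazard ratio 1.41 / 1.41, power 89.1% / 89.2%
- shapes 1.5 and 1.2: 1.39 / 1.40, power 84.7% / 86.6%
- hysterectomy shape 2, median 7 weeks, and colectomy shape 1, median 14 weeks: 1.36 / 1.40, power 81.0% / 85.5%, null rejection 3.1% / 4.3%.

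**Late tail within colectomy.** Assumptions: shape 1.5; medians 7 weeks (hysterectomy), 10 weeks (colectomy) and 30 weeks for a delayed 30% of colectomies; hazard ratio 1.4 within the delayed and undelayed groups. Result: 1.32 / 1.33, power 73% / 75%; a repeat gave 71% / 73%. Stratifying moves the estimate by only 0.01, and most of the distance from 1.40 remains.

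**The case against.** Adjusting for stratification factors as covariates is accepted practice, and in these simulations it did as well as or better than the crude model within simulation error (for shapes 1.0/2.0 at a 50% share, 76.9% power against 70.3% crude). That stands: the sentence is not wrong.

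The curve shapes are assumed. The article's own literature review found little on time to full recovery after major abdominal surgery, and it reports no curve by procedure. The pair that produces the loss of about 5 points is not obviously realistic either: with shapes 1 and 2 and medians 12 and 8 weeks, 1 − 2^(−2/12) = 11% of colectomy controls but only 1 − 2^(−(2/8)²) = 4% of hysterectomy controls would have resumed everything by week 2. The procedure mix is also not given; counts of surgical and gynaecological practices are not counts of patients. This stands, and it limits the point to a conditional one.

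A reader might infer that cancer, chemotherapy and stoma care show the hazards to be non-proportional, and that stratifying by procedure repairs the damage. The documents do not support this. They show clinical difference, not curve shape, and a chemotherapy tail lies inside the colectomy stratum, where separate baselines by procedure gain only about 2 points.

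A reader might also infer that the trial's deciding test loses power. The article does not say that the adjusted model decides, and it sizes the trial on a log-rank test.

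The planned subgroup analyses by procedure could reveal different curves, but they do not give the overall adjusted hazard ratio. A check of proportionality may sit in an analysis plan not shown, so its absence is not held against the article. The covariate form, however, is stated.

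**Conclusion.** This is an optional improvement, not an error. The adjusted model for the primary outcome rests on proportional recovery hazards between two unlike procedures, and the documents neither support nor refute that.

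Under a common within-procedure hazard ratio of 1.4 and the assumed Weibull shapes, the covariate model estimates about 1.36 to 1.40. Its power loss against a procedure-stratified model runs from nothing (proportional hazards) through 1 to 3 points (mild or reversed differences) to about 5 (shapes 1 and 2; single runs 4 to 6). Losses of 7 to 9 points appear only with the more extreme pair 0.8/2.5. Under marked differences the test tends to be conservative, so the risk is a missed or understated effect rather than a false positive. Stratifying never cost more than simulation noise.

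**What to change.** Reword the sentence on the adjusted analysis: *The adjusted Cox model will be stratified by surgical procedure (separate baseline hazards), with hospital and sex as covariates.* SPSS, the named software, offers this through the STRATA option of its Cox procedure.

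The cost is one line of wording, settled before the analysis. The model no longer yields a hazard ratio for procedure itself, which is not a study question. The change should not be presented as a remedy for differences within colectomy, which it leaves in place.

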#### Review of the Literature

The systematic review included 27 studies that focused on replacing or complementing perioperative usual care with some form of care via information and communication technology (ICT) such as telemonitoring, telerehabilitation, teleconsultation, or an educational or supportive website in various types of surgery. Of these studies, 92% reported at least an equal or positive effect of the eHealth intervention compared with usual care on patient-related outcomes. The results show that eHealth or other forms of ICT and telehealth improve clinical outcomes, knowledge, and satisfaction of patients undergoing various forms of surgery. Furthermore, eHealth improves RTW and daily functioning after surgery. Positive influencing factors on these patient-related outcomes were (1) easy access to the intervention, (2) expectation management, and (3) a combined symptom monitoring by blended care [27].

The literature search in the IM protocol article of Vonk Noordegraaf et al identified that pain and discomfort, feelings of fear, and infections were delaying factors for RTW [19]. In addition, literature showed that the substantial variation in convalescence recommendations given by health care professionals were also of influence on the total duration of sickness absence [9,30]. In the broadened search, a wide variety in convalescence duration after minor general surgical procedures (eg, cholecystectomy and hernia inguinal repairs) was observed [31,32]. For major abdominal procedures, limited research was available to analyze the time of full recovery including RNA (and RTW) [33-36]. However, literature does show that the total duration of convalescence was longer than expected despite the implementation of minimal invasive techniques and ERAS programs applied by major abdominal procedures [1,37,38]. Duration of convalescence depends on pain, complications, or fear of recurrence (in case of cancer of hernia inguinal repairs) [39-41]. Preoperative expectations of convalescence, size of the incision, and fatigue were important contributory factors to explain actual convalescence [39-42]. Furthermore, patients who were physically active after colorectal surgery were more likely to recover faster [43].

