#### Outcome Measures

Our primary outcome measure is RNA. The Patient-Reported Outcomes Measurement Information System physical functioning item bank version 1.2 will be used to measure limitations in daily activities. A list of 29 most relevant selected activities will be presented to participants before surgery with the goal to select 8 activities, which are most relevant for them in their daily life. They will be asked in the following questionnaires after surgery if they can already perform one of these 8 activities. RNA is defined as the time in calendar days from the day of surgery until a participant has resumed all activities [57,58].

Secondary outcomes are social participation, self-rated health, duration until RTW, physical activity, length of recovery, pain intensity, and patient satisfaction [59-63]. Costs will be measured from a societal and health care perspective and consist of costs of the intervention, health care utilization costs, and costs associated with lost productivity [64,65]. Sociodemographic data and questions regarding expectations about the length of recovery and the amount of anxiety will be assessed at the baseline measurement. Complications will be assessed by reviewing the surgical reports and postoperative notes and scored by using the Clavien-Dindo classification [66]. The outcome measures will be obtained by using questionnaires administered at baseline (approximately 1-2 week preoperative) and at 2, 4, and 6 weeks and 3, 6, 9, and 12 months after surgery. For a total overview of all outcomes per measurement moment of this study, see Multimedia Appendix 5.

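### The primary outcome has two unranked analyses, crude and adjusted, and an open-ended rule that adds covariates after the data are seen, so the model behind the headline hazard ratio is not fixed

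*Protocol article*

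**What the plan says.** All of this is in Step 6 of the protocol article.

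- **Outcome Measures:** "RNA is defined as the time in calendar days from the day of surgery until a participant has resumed all activities". A hazard ratio above 1 therefore means faster recovery. The section also says that "questions regarding expectations about the length of recovery and the amount of anxiety will be assessed at the baseline measurement".
- **Data Analyses Plan, primary analysis:** the primary outcome "will be analyzed by both crude and adjusted survival analyses". The adjusted version contains hospital, surgical procedure and sex, because randomisation was stratified by them. Neither version is called primary.
- **Data Analyses Plan, further covariates:** "Adjustments will be made if there are clinically relevant differences between the intervention and the control group in the baseline characteristics". The sentence continues with a second trigger, the observation of other possible confounders. It gives no candidate list and no threshold. The same paragraph plans between-arm tests of baseline characteristics.
- **Sample Size Calculation:** "To detect a hazard ratio of 1.4 for RNA" is the aim, "with 80% power while testing using a 2-sided log-rank test". No covariates are mentioned, and the log-rank test is not called the primary analysis.
- **Recruitment, Inclusion, Allocation, and Blinding of Patients:** the researchers who analyse the data are blinded to allocation.

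**The concern.** Three things are fixed badly.

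1. **Two answers, no ranking.** A crude and a covariate-adjusted Cox hazard ratio are different quantities when the covariates are prognostic, even with perfect balance. If the two fall on either side of significance, the plan does not say which one is the result.
2. **The wrong criterion for covariates.** With randomised arms, a baseline difference is chance. What a covariate contributes depends on how strongly it predicts recovery, not on whether it happens to be unbalanced.
3. **An open second trigger.** As worded, it is not restricted to variables measured before randomisation, so it would permit adjustment for something the intervention may have changed.

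A suitable covariate is at hand. The Review of the Literature reports: "Preoperative expectations of convalescence, size of the incision, and fatigue were important contributory factors to explain actual convalescence". Recovery expectations are recorded at baseline, yet the plan would use them only if one of the triggers is met.

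At stake is whether the headline estimate and p-value come from a model chosen before or after the data were seen.

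**Working it through.** **The plan's own figure.** The Sample Size Calculation states that "at a significance level of 5%, a total of 318 events need to be observed". By Schoenfeld's formula, events = 4(z₁₋α/₂ + z₁₋β)² / (ln HR)², with ln 1.4 = 0.3365:

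- 80% power: 4 × (1.960 + 0.842)² / 0.1132 = 278 (Freedman's formula gives 283).
- 85% power: 4 × (1.960 + 1.036)² / 0.1132 = 318.

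So 318 does not follow from the stated 80% but matches 85%. This is a separate matter, and it makes the trial larger, not smaller. It is needed here only as a reference for the powers below.

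**Size of the present point.** The documents give no covariate effects, so this was simulated over an assumed range, with 3,500 trials per scenario.

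- *From the documents:* 354 patients, 1:1 allocation, blocks of 2 within hospital, sex and procedure, 18 departments in 11 hospitals, control median 10 weeks, 12-month follow-up, 10% dropout.
- *Assumed:* conditional HR 1.4; hospital variation with SD 0.2 on the log hazard; procedure HR from 1 to 3; six further baseline variables, three of them prognostic (HR from 1 to 1.3 per SD); a variable is added when its standardised difference exceeds 0.15. The plan gives no threshold, so this stands in for its clinical-relevance criterion.

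Four Cox models were compared: (A) crude; (B) hospital, procedure and sex; (C) B plus the variables found unbalanced; (D) B plus all six variables, fixed in advance.

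Power at conditional HR 1.4, in %:

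| Procedure HR / covariate HR per SD | A | B | C | D |
|---|---|---|---|---|
| 1 / 1 | 85.3 | 87.2 | 86.9 | 87.1 |
| 1.5 / 1.2 | 78.4 | 81.1 | 82.5 | 86.4 |
| 2 / 1.2 | 74.0 | 82.2 | 82.4 | 86.6 |
| 3 / 1.3 | 64.1 | 77.4 | 79.1 | 85.7 |

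Check on the first row: it had 339 events on average, and Φ(√339/2 × 0.3365 − 1.96) = Φ(1.14) = 0.87, in line with 85–87%.

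Rejection rate under no effect, in %:

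| Procedure HR / covariate HR per SD | A | B | C | D | Best of A, B | Best of A, B, C |
|---|---|---|---|---|---|---|
| 1 / 1 | 4.8 | 5.7 | 5.8 | 6.0 | 6.4 | 6.7 |
| 1.5 / 1.2 | 4.5 | 6.0 | 6.1 | 7.3 | 6.8 | 7.8 |
| 2 / 1.2 | 4.3 | 6.1 | 5.7 | 6.1 | 6.9 | 7.6 |
| 3 / 1.3 | 3.2 | 5.9 | 5.2 | 5.9 | 6.6 | 7.5 |

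The simulation error is about √(0.05 × 0.95/3500) = 0.4 points here and about √(0.8 × 0.2/3500) = 0.7 points for power.

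**Reading the tables.**

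- *Rule against fixed covariates (D − C):* 86.4 − 82.5 = 3.9, 86.6 − 82.4 = 4.2 and 85.7 − 79.1 = 6.6, so about 4–7 points. The powers are not corrected for size. D's null rate exceeds C's by 0.4–1.2 points in these rows, so part of the gain is excess rejection by the largest model. That is a reason to keep the list short.
- *Rule against A or B:* no loss beyond simulation error.
- *Crude against stratification-adjusted (B − A):* 2.7 to 13.3 points when there are prognostic effects, and 1.9 with none.
- *Free choice of model:* over B alone, the best of two adds 0.7–0.8 points and the best of three adds 1.0–1.8.
- *Estimate:* at procedure HR 2 the mean hazard ratio is 1.33 (A), 1.39 (B), 1.39 (C) and 1.43 (D).

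**The case against.** **Detail left to an analysis plan.** This is one paragraph of an intervention-development article, and the ranking of models and a covariate list commonly stand in a fuller document that is not shown. That is fair for anything merely absent. It does not cover the conditional rule, which is stated, nor the pair of analyses, which is presented as the plan for the primary outcome.

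**Safeguards.** Hospital, procedure and sex are prespecified in the adjusted model, and the analysts are blinded to allocation. Both count. Blinding limits choosing a model by the direction of the effect. It does not fix the model, since p-values can be compared with coded arms.

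**Stronger readings that a reader might infer, and that the documents do not support:**

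- *That the covariate rule costs power outright.* It does so only against prognostic covariates fixed in advance.
- *That the trial is underpowered.* With stronger assumptions (procedure HR 0.5, one covariate with log-HR 0.5 per SD, conditional HR 1.4), crude power falls to 66%, with a crude HR of 1.30. But the Sample Size Calculation attaches 1.4 to a log-rank test without covariates. If the conditional HR is set to 1.5, the crude HR is 1.39, near the plan's figure, and crude power is 86%. The same caution applies to column A above. The relative gain from adjustment remains, but a shortfall against the design target is not shown.
- *That a significant baseline test triggers adjustment.* The plan speaks of clinical relevance and does not link the tests to the decision.
- *That every prognostic factor named in the literature review is available.* Of expectations, incision size and fatigue, Outcome Measures names only expectations as assessed at baseline.

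**Conclusion.** The point holds in this form: the text leaves two primary analyses unranked and adds covariates by a data-dependent rule with no list, no threshold and no restriction to baseline variables. The headline hazard ratio therefore depends on a model that is not fixed.

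The size is modest and depends on assumptions. Type I error under free choice is about 6.4–7.8%, most of which is the adjusted model's own 5.7–6.1%. The upper figures assume that the most favourable result is always taken, which the plan nowhere proposes. The power given up against fixed prognostic covariates is about 4–7 points under the assumed effects. With no procedure or covariate effects all four models perform alike.

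This should be fixed. It does not by itself invalidate the design.

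**What to change.** - Name one primary analysis: a Cox model that accounts for hospital, procedure and sex, plus a short list of baseline covariates fixed before unblinding. Draw the list from what Outcome Measures says is collected, for example expected length of recovery, and age from the sociodemographic data. A baseline physical function score should be listed only if it is confirmed as collected. Benign or malignant indication needs care: Eligibility Criteria exclude malignancy for hysterectomy, so it varies only within colectomy.
- Call the crude analysis supportive.
- Delete the conditional adjustment sentence, including its second trigger, and the between-arm tests of baseline characteristics. Keep the descriptive baseline table.
- State how the test in the Sample Size Calculation relates to the named model.

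The cost is a few sentences and no new data. There are two downsides. The covariate list must be settled before unblinding. The adjusted hazard ratio is a conditional effect, not directly the log-rank hazard ratio used for the sample size, so the report should say which is meant.
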